Design: A: multi center prospective pre-test posttest study; B: single center prospective pretest and posttest study; C: single center retrospective pretest and prospective posttest group, interrupted time series design; D: single center retrospective pretest and prospective posttest group, time series design; E: multicenter, prospective pretest and posttest group, time series; F: multicenter retrospective pretest and posttest group, interrupted time series; G: single center cohort study; 1++ High-quality meta-analyses, systematic reviews of RCTs, or RCTs with a very low risk of bias; 1+ Well-conducted meta-analyses, systematic reviews of RCTs, or RCTs with a low risk of bias; 1- Meta-analyses, systematic reviews of RCTs, or RCTs with a high risk of bias; 2++ High-quality systematic reviews of case–control or cohort studies, or high-quality case–control or cohort studies with a very low risk of confounding, bias, or chance and a high probability that the relationship is causal; 2+ Well-conducted case–control or cohort studies with a low risk of confounding, bias, or chance and a moderate probability that the relationship is causal; 2- Case–control or cohort studies with a high risk of confounding, bias or chance, and a significant probability that the relationship is not causal; 3 Non-analytic studies; for example, case reports, case series; 4 Expert opinion.

*CVC* central venous catheter, *BSI* bloodstream infection, *NICU* neonatal intensive care unit, *PICU* pediatric critical care unit.

^#^Premature born infants with birth weight < 1500 grams; and *indicate significant reduction of bloodstream infections per 1000 line-days.

**Table 2 T2:** Major components of CVC insertion bundle and maintenance bundle in The Erasmus MC-Sophia Children’s Hospital

**Insertion bundle**	**Components**
Strict hand hygiene according to “my 5 moments”^#^	
Full sterile barrier	Hygienic precaution training for all healthcare workers who insert CVCs
	Sterile gown, mask, hat, double sterile gloves worn by the healthcare worker who inserts the CVC
	Use of pre-packaged CVC insertion kit
	Sterile drape covering the patient for least 80%
Physical barrier between the environment and the child, insertion cart, and healthcare worker who inserts the CVC	
Insertion site cleaned with alcohol 70% with chlorhexidine 0.5% (chlorhexedine 0.2% in water for infants < 26 weeks gestational age)	

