Use of a timer displayed at the bedside’s screen to secure an air dry time of at least 30 seconds	
Use a new needle after each attempt to insert a CVC through the intact skin	
Chlorhexedine impregnated sponge attached at insertion site (not in infants < 40 weeks gestational age)	

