#### ***Measuring***

The outcome measure is the number of CA-BSIs per 1000 line-days, calculated by dividing the number of bloodstream infections by the risk-adjusted denominator 1000 line-days. As a baseline measurement we prospectively collected data from 1st January 2011 to 1st January 2012. Over that period the number of CA-BSIs per 1000 line-days was 11.2 at the neonatal intensive care unit and 7.9 at the pediatric intensive care unit.

As secondary outcome (process measures) we selected degree of adherence to safety procedures, e.g. maximum sterile barrier during the CVC insertion procedure and adherence to hygienic protocols during intravenous administration. Adherence will be documented with the use of two observation tools (Tables 3 and 4). Performance related to the insertion procedure will be measured with two tools: use of the time out procedure that is linked with the CVC insertion protocol (Additional file 1: Table S1) and a questionnaire daily popping up in the patient’s electronic record informing after signs of infection at insertion site as well as the need of having the CVC in place.

**Table 3 T3:** Process indicators CVC insertion monitoring form

	**Process indicator**	**Satisfied**
1	Skin cleaned with alcohol 70% with chlorhexidine 0.2%; or chlorhexidine 0.2% in water in infants with a gestational age < 26 weeks	Yes O No O
2	Air dry of at least 30 seconds after skin preparation prior to guide-wire insertion	Yes O No O
3	New needle used after each attempt to insert a CVC through the intact skin	Yes O No O
4	Sterile drape covering the patient for least 80%	Yes O No O
5	The provider inserting the CVC used maximum sterile barrier e.g. sterile gown, double sterile gloves, mask, and hat	Yes O No O
6	Optimal insertion site was selected or another site was argued for	Yes O No O
7	Echo use during insertion of jugularis and subclavia catheter	Yes O No O
8	Chlorhexidine impregnated sponge used in infants < 40 weeks gestational age	Yes O No O

*CVC* central venous catheter.

**Table 4 T4:** Process indicators CVC nursing care monitoring form

	**Process indicator**	**Satisfied**
1	Appropriate hand hygiene prior to preparation of intravenous medication	Yes O No O
2	Disinfection of the cap or ampoule’s surface using alcohol 70%	Yes O No O
3	Applying 30 seconds air drying time after disinfection ampoule’s surface	Yes O No O
4	Disinfection of connector with alcohol 70%^#^	Yes O No O

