### Secondary outcomes

Rate of adherence to the CVC insertion bundle and rate of adherence to the maintenance bundle will serve as secondary outcomes.

The attending nurse will assess adherence to the CVC insertion bundle during the insertion procedure (Table 3). To this aim we designed a digital tab with drop-down menu for the two different patient data management systems. The time out procedure prior to the CVC insertion is predominantly added for creating safety awareness during insertion (Additional file 1: Table S1). During the insertion procedure all involved healthcare workers are encouraged to make comments and to stop the procedure in case of violation of insertion bundle. Intravenous medication preparation and administration items will serve to measure adherence to the CVC maintenance bundle (Table 4). Purpose-trained nurses will randomly assess these items during planned daily care.

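### Items 8 and 1 of the insertion monitoring form (Table 3) disagree with the insertion bundle (Table 2) whose adherence the form is meant to score

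*Protocol article*

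**What the plan says.** The bundle is set out in Table 2 (Collecting evidence). For skin cleaning it has "Insertion site cleaned with alcohol 70% with chlorhexidine 0.5" per cent, with 0.2% in water for infants below 26 weeks' gestation. For the sponge it has "Chlorhexedine impregnated sponge attached at insertion site (not in infants < 40 weeks gestational age".

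The form is Table 3 (Measuring), with a Yes/No answer per item. Item 1 is "Skin cleaned with alcohol 70% with chlorhexidine 0.2%; or chlorhexidine 0.2% in water in infants with a gestational age < 26 weeks". Item 8 is "Chlorhexidine impregnated sponge used in infants < 40 weeks gestational age".

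The link between form and outcome is explicit. Measuring says "Adherence will be documented with the use of two observation tools (Tables 3 and 4". Secondary outcomes says "The attending nurse will assess adherence to the CVC insertion bundle during the insertion procedure (Table 3", and adds "To this aim we designed a digital tab with drop-down menu for the two different patient data management systems". The same section makes the insertion-bundle adherence rate a secondary outcome. Table 5 lists it for quarterly feedback. The Sample size section gives an estimated baseline of 60% and a post-intervention aim of 100%.

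**The concern.** An adherence form should say Yes when the bundle was followed and No when it was not. On two items the printed form does something else. Item 8 credits the sponge in the one group where Table 2 rules it out, and is silent on the group where Table 2 calls for it. Item 1 asks for a different antiseptic strength from the one in Table 2 for every patient of 26 weeks or more.

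What is at stake is one secondary outcome and its use during the study. The rate is returned to wards each quarter so that they can find flaws and adjust. A form that disagrees with the bundle could report correct practice as a lapse and, on item 8, could favour a practice that the bundle excludes. The project's stated purpose is to replace differing ward protocols with one standard, so the standard and its scoring form need to agree.

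**Working it through.** **The plan's own figure.** The Sample size section states 15 insertion observations per period for 60% against 100%, alpha 0.05, power 0.8. Sidedness is not stated; assuming two-sided, with pooled variance under the null and no continuity correction:

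n = [1.96 × √(2 × 0.8 × 0.2) + 0.8416 × √(0.6 × 0.4 + 1.0 × 0)]² / 0.4² = (1.109 + 0.412)² / 0.16 = 14.5, rounded up to 15.

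The figure reproduces. The wording of items 1 and 8 is not an input to it. It affects only what counts as adherent.

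**Item by item, Table 3 against Table 2.**

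| Table 3 item | Table 2 | Result |
|---|---|---|
| 1 Skin antiseptic: 0.2% in alcohol 70%; 0.2% in water below 26 weeks | 0.5% in alcohol 70%; 0.2% in water below 26 weeks | Disagrees at 26 weeks or more |
| 2 Air drying, 30 seconds | Same | Agrees |
| 3 New needle per attempt | "Use a new needle after each attempt to insert a CVC through the intact skin" | Agrees |
| 4 Drape, 80% | Same | Agrees |
| 5 Gown, double gloves, mask, hat | Same | Agrees |
| 6 Site selection | No counterpart | Not comparable |
| 7 Echo use | No counterpart | Not comparable |
| 8 Sponge used below 40 weeks | Sponge used, but not below 40 weeks | Disagrees |

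Four items agree, two disagree and two have no counterpart, so 2 of the 6 comparable items disagree. Table 2 lists only the main components, so items 6 and 7 are not criticised.

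**An insertion that fully complies with Table 2, scored literally on the printed form.**

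- Below 26 weeks: item 1 Yes (0.2% in water). Item 8 No, because the sponge was rightly omitted.
- 26 to below 40 weeks: item 1 No, because 0.5% was used. Item 8 No.
- 40 weeks or more: item 1 No. Item 8 is not addressed by its wording. With only Yes and No on offer, the nurse might tick either or leave it blank.

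Every age band has at least one No. This describes the wording. It is not a frequency, because the age mix is unknown.

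**Effect on a rate.** The article gives no scoring rule. If an insertion counted as adherent only when every item was Yes, no fully compliant insertion would pass. If the eight items were weighted equally and all others were Yes, the score would be 7/8 = 87.5% with one item failed and 6/8 = 75% with both. The answer depends on an unstated rule, so these are illustrations. Under either rule the 100% target cannot be met by practice that follows Table 2.

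**The case against.** The strongest objection is that the effect on data is unproven. Scoring takes place in a digital tab and, under Data collection, on an observers' case report form. Neither is shown. Both discrepancies look like drafting slips, and the working forms may be correct. This stands: a reader might infer that the adherence data will be mis-scored, or that wards will be told correct practice is a failure, but the article supports only the conditional statement.

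A reader might also infer that Table 3 is the wrong one of the two. The document does not settle that. It shows that the tables disagree, and the scoring above takes Table 2 as the reference only because it defines the bundle.

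The Measuring section also names a time-out procedure and a daily electronic questionnaire as measures of insertion performance. This has limited force, because Secondary outcomes ties insertion-bundle adherence to Table 3 and describes the time-out mainly as a way to raise awareness.

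The protocol still needed steering-committee approval, so a review step exists. The text does not say that this step covers the monitoring form.

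Finally, the two items differ in weight. Item 8 inverts an age exclusion. Item 1 is a single figure in one branch, and whether an observer would answer No on concentration alone is unknown. That is a fair reason to put item 8 first, but not to leave item 1 uncorrected.

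**Conclusion.** The point holds as a disagreement between the bundle and its named scoring form. It is certain on the text, affects 2 of 6 comparable items and is reconciled nowhere in the article. Item 8 is the more serious.

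The consequence for the data is conditional on the digital tab and the observers' form carrying the printed wording, and on literal scoring. Under those conditions, Table 2-compliant practice receives at least one No at every gestational age, a composite rate that includes these items cannot reach 100%, and quarterly feedback could mislead. The size of any bias cannot be stated, because neither the scoring rule nor the age mix is given.

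The primary outcome, its analysis and both sample-size calculations are untouched. No view is taken on which clinical wording is right. The matter should be fixed, but it concerns one secondary process outcome.

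**What to change.** The steering committee confirms the intended rule for the antiseptic and the sponge. The same wording then goes into the bundle, Table 3, the drop-downs in both patient data management systems and the observers' case report form.

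If Table 2 is right:

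- Item 1 asks for 70% alcohol containing 0.5% chlorhexidine, or 0.2% aqueous chlorhexidine when gestational age is under 26 weeks.
- Item 8 asks whether the sponge was applied, states that it is not to be used under 40 weeks, and gains a not-applicable option.

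The article does not say that any insertion has yet been scored on this form. If any was scored on conflicting wording, items 1 and 8 are left out of the adherence rate for that insertion unless the patient record shows which antiseptic was used or whether a sponge was applied. Recorded answers should not be reversed. The column is headed as satisfied or not, so a nurse who knew the bundle may have ticked Yes below 40 weeks for a correct omission, and reversal would turn a correct record into an error.

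The cost is rewording two items in a few places, with no extra patients or observations. At worst, items 1 and 8 are lost for insertions already scored that cannot be verified.

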#### ***Implementation strategies***

*Engage*. We will inform all stakeholders and senior management staff about the current high number of CA-BSIs per 1000 line-days and the need to reduce this number, and address the undesirability of having different CVC protocols in place – implying we need to implement general preventive measures hospital-wide. Representative stakeholders from all wards will be invited to join the steering committee. Final approval of the CVC protocol by the steering committee is required and the members will support implementation in their respective wards and operation room suite.

Table 5 provides an overview of proposed implementation strategies. Strategies for the dissemination of knowledge are based on the Pronovost-model and others [12,24,25].

**Table 5 T5:** Selected implementation strategies

**Intervention types**	**Components**
Education program, theme week	Multidisciplinary seminar
	Workshop for physicians
	Instruction for nurses
	Instruction on hygienic insertion and maintenance
Reminders	Leaflets
	Screen savers
	Daily questionnaire CVC need, pop-up in electronic patient management system
	Sticker attached at disinfection solution: apply 30 seconds air dry time
Feedback (quarterly)	Reporting incidence of CA-BSI
	Reporting adherence to insertion bundle
	Reporting adherence to maintenance bundle
Engagement of the managing staff	One-liners combined with picture
Awareness	Time out procedure, and staff empowerment to stop in case of protocol violation
	Daily goal sheet
Procedures	Revised protocols
	CVC infection preventions manual.
	Timers
	30 seconds air dry timer displayed on bedside screen

*CA-BSI* catheter-associated bloodstream infection, *CVC* central venous catheter.

*Engage & educate*. To improve engagement and education level we will organise a hospital-wide theme week dedicated to CA-BSIs reduction. Events are aimed at educating all staff involved on the new CVC protocol and CVC infection prevention manual and persuading them to change their usual care and comply with the new protocol. Two weeks prior, posters announcing the program will be spread, provided with supportive one-liners from senior management and senior clinical leaders including their portraits [26]. The key players fully supporting the new protocol will act as role models for more junior colleagues. During the CVC week, flyers presenting the key players’ one-liners and the on-liner messages will be used as screen savers throughout the children’s hospital [27].

A tentative schedule is the following:

Monday; flyer distribution, informative mini-symposium, marking of ten potential dirty surfaces at each ward, attaching a sticker on them and culturing the surfaces.

Tuesday; nurses visit bacterial laboratory and the new guidelines are discussed;

Wednesday; physicians and nurse practitioners receive clinical instructions; tables in the staff restaurant are decked out with placemats asking questions on appropriate CVC care; lecture on reasons for non-adherence to hand hygiene protocols.

Thursday; clinical instructions and lecture to promote high adherence to documenting CVC data in the patient data management system.

Friday, theme week wrap-up with musical act during lunch-time in the staff restaurant and a closing ceremony.

Detailed information concerning the infection prevention week is supplemented at Additional file 2.

For educational purposes we will use several types of reminders, such as screen savers; stickers attached on disinfection solution bottles displaying the message: “apply 30 seconds air dry time”; infection prevention messages printed on toilet paper. Furthermore, if a CVC is in situ, a questionnaire will daily pop up in the patient’s record in the electronic patient data management system. The questionnaire addresses the following items: “Is the transparent dressing in good order?”; “Is there any redness near the insertion place?”; and “Is the CVC still needed?”. The response categories will be collected at nominal level e.g. yes or no.

*Evaluate*. Quarterly, the primary and secondary outcomes will be measured to evaluate whether the intervention is successful and to identify possible flaws. The information obtained may serve as input for additional improvements. Data will be compared to the baseline measurement data and data collected in the previous period, if applicable, by interrupted time series analysis. Findings will be reported to the directors of the children’s hospital. Furthermore, findings on ward level will be presented to the management of the relevant ward. For steering purposes we will make use of insightful graphs and tables. Successful outcomes may be an incentive to continue on the road we have taken; negative outcomes may be an incentive to increase efforts.

*Endure and extend*. Pronovost and colleagues later added this idem to their model [12]. We postulate that the daily questioning on the need to have the CVC in place, as sketched above, will create awareness of safety precautions. Furthermore, we presume that sharing of the quarterly performance outcomes will improve perceptions of safe patient care. Finally, encouraging open discussion about possible procedure flaws and potential improvements will benefit the CVC process at large [25].

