**Methods/design:**

An interrupted time series design will be used; the study will encompass all children who need a central venous catheter. New state-of-the-art central venous catheter bundles will be developed. The Pronovost-model will guide the implementation process. We developed a tailored multifaceted implementation strategy consisting of reminders, feedback, management support, local opinion leaders, and education. Primary outcome measure is the number of catheter-associated infections per 1000 line-days. The process outcome is degree of adherence to use of these central venous catheter bundles is the secondary outcome. A cost-effectiveness analysis is part of the study. Outcomes will be monitored during three periods: baseline, pre-intervention, and post-intervention for over 48 months.

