### Sample size

For the power analysis we made some simplifying assumptions: only pre- and post-intervention periods are compared and instead of comparing slopes we compare levels of infection rate. Under these circumstances a length of 1.9 years before and after intervention (leading to an assumed number of 141 cases before) is enough to detect a drop in rate to 70%. When we apply loglinear regression analysis with Poisson error distribution corrected for number of days at risk we find that that two times 1.9 years leads to a power of 80%.

The baseline rates of adherence to the insertion and maintenance bundles are estimated at 60% and 20%, respectively; the post intervention rates aimed at are 100% and 45%, respectively. Sample size calculation indicated that each sequential period requires 15 insertion observations and 45 maintenance observations to detect a relative difference of 37% and 125% alpha of 0.05 and a 1-beta of 0.8.

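### The stated 80% power for adherence is not the power of the interrupted time series analysis named for it, and 45 maintenance observations give only about 72% even in a simple two-sided comparison

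*Protocol article*

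**What the plan says.** The Evaluate paragraph of Implementation strategies states: "Quarterly, the primary and secondary outcomes will be measured to evaluate whether the intervention is successful". Shortly afterwards it names the method: "Data will be compared to the baseline measurement data and data collected in the previous period, if applicable, by interrupted time series analysis". The Secondary outcomes section lists adherence to the insertion bundle and to the maintenance bundle, so the data in question include adherence. The article names no other comparison method for adherence.

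The Sample size section gives the adherence inputs: "The baseline rates of adherence to the insertion and maintenance bundles are estimated at 60% and 20%, respectively", and "the post intervention rates aimed at are 100% and 45%, respectively". It concludes that "each sequential period requires 15 insertion observations and 45 maintenance observations" "to detect a relative difference of 37% and 125"%, at "alpha of 0.05 and a 1-beta of 0.8". It names no test, no sidedness and no number of periods.

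Two other places bear on the point. The Statistical analysis section describes a three-segment loglinear model, but words it for the infection rate. The Sample size section openly replaces slopes by pre/post levels, but says so for the infection rate only; the adherence figures follow in a separate paragraph without that remark.

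**The concern.** A segmented analysis has to estimate a pre-intervention trend and then a departure from it. That needs many more observations than comparing two proportions. If adherence is judged by such a model, the printed 80% does not describe the chance of detecting the targeted gain.

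The meaning of the sampling unit adds to the problem. The Abstract counts phases as periods ("Outcomes will be monitored during three periods: baseline, pre-intervention, and post-intervention for over 48 months"), while Study design and Statistical analysis also use the word for three-month blocks. So 15 and 45 may be totals per phase or numbers per quarter.

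Objectives 2 and 3, and the part of the hypothesis that concerns adherence, rest on this comparison. A real improvement could be reported as no detectable change, or a null result could be read as if the study had 80% power.

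**Working it through.** **1. The plan's own figures, as a two-period comparison.** Inputs are from Sample size: 60% to 100% with n = 15; 20% to 45% with n = 45; alpha 0.05; power 0.80. The pooled normal formula, with p̄ the mean of the two rates, is

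n = [z_α √(2p̄(1−p̄)) + 0.8416 √(p0(1−p0) + p1(1−p1))]² / (p1−p0)².

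- Insertion, two-sided: p̄ = 0.80. n = (1.96 × 0.5657 + 0.8416 × 0.4899)² / 0.16 = 14.5, so 15. This matches. Power with 15: Φ[(0.40 × √15 − 1.1087)/0.4899] = Φ(0.90) = 82%.
- Maintenance, two-sided: p̄ = 0.325. n = (1.96 × 0.6624 + 0.8416 × 0.6384)² / 0.0625 = 53.9, so 54. This does not match 45. Power with 45: Φ[(0.25 × √45 − 1.2983)/0.6384] = Φ(0.59) = 72%.
- One-sided (z = 1.645): maintenance needs 43, and 45 gives 82%. Insertion then needs only 12, not 15.

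No single variant tried (pooled, unpooled, continuity-corrected or arcsine, one- or two-sided) reproduces both figures at the stated rates. The printed relative differences do not settle it. From 20% to 45% is +125%, which agrees; from 60% to 100% is +67%, not 37%. If 37 is read as percentage points (60% to 97%), the one-sided pooled formula gives 15 and 43, close to the printed pair. Sidedness therefore cannot be inferred with confidence.

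**2. The same observations under a segmented model.** The article specifies no adherence model, so this one is an assumption: logistic regression on quarterly binomial counts, with intercept, time, and a level and slope change for each later segment. Observations are independent, there is no true trend, and adherence during any intervention segment is midway between the two rates. The test is a two-sided Wald test of the level change at the start of the post-intervention segment. The true effect for maintenance is logit(0.45) − logit(0.20) = 1.186. Power = Φ(1.186/SE − 1.96) + Φ(−1.186/SE − 1.96), with SE from the expected information matrix.

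The layouts each total 16 quarters (48 months); how they divide is assumed.

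| Quarters (pre + intervention + post) | 45 per phase: SE, power | 45 per quarter: SE, power |
|---|---|---|
| 8 + 0 + 8 | 0.987, 22% | 0.349, 92% |
| 7 + 2 + 7 | 1.296, 15% | 0.490, 68% |
| 4 + 4 + 8 | 2.266, 8% | 1.116, 19% |

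With 45 per phase and no trend terms, the same logistic model has SE 0.478 and power 70%, close to the 72% above. The loss from there to 8-22% is the price of estimating trends.

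**3. Insertion under the same model.** A rate of 100% has no finite logit, so 97% is used; the Wald test is conservative this near the boundary. With 15 per phase, power is about 18%, 16% and 11% for the three layouts. With 15 per quarter it is about 83%, 72% and 39%.

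**The case against.** The strongest reply is that time series analysis is not firmly fixed for adherence. The sentence sits in a paragraph about quarterly feedback to directors and ward management, and it carries the words 'if applicable'. The Statistical analysis section ties the segmented model to the infection rate, and a condensed article may leave the adherence test to a fuller document. This stands in part: the premise is a literal reading. But the hedge most naturally concerns the previous period's data, which do not exist at the first comparison, and no other adherence comparison is offered. The mismatch lies between two printed statements and does not depend on missing detail.

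Three stronger readings are tempting, and the document does not support them.

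- A reader might infer that the analysis would miss the targeted gain most of the time. That holds only if the sampling period is a phase. With 45 per quarter and two segments, maintenance power is about 92%.
- A reader might infer that observations will be as sparse as 15 or 45 spread over a phase. The figures are stated as requirements. Data collection plans random observations around the clock, and Secondary outcomes has the attending nurse record insertions; neither sets a cap.
- A reader might infer that both sizes come from one ordinary two-proportion formula. Step 1 of the working shows that 45 does not follow from the two-sided version that gives 15.

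It is also fair to say that a plain before-after comparison gives up the trend correction that the article values. That is a real, though small, cost of the fix.

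**Conclusion.** The concern holds in limited form. The printed 80% for adherence is not the power of the only comparison method that the article names for these outcomes. For maintenance, level-change power is about 8-22% if 45 is per phase and about 19-92% if it is per quarter. Both three-segment layouts in the table stay below 80% on either reading; only the two-segment, per-quarter case exceeds it. These figures rest on the assumed model, independent observations, no true trend and assumed phase lengths.

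The arithmetic of the two-period comparison needs fewer assumptions: two-sided, 45 gives about 72% power and 54 are needed, while 15 for insertion gives about 82%. It would therefore be wrong to repair the text merely by saying that the 80% belongs to a before-after comparison, because for maintenance that is true only if the test is one-sided. The point affects secondary outcomes and leaves the infection-rate analysis untouched.

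**What to change.** - **Evaluate paragraph and Statistical analysis:** for objectives 2 and 3, name the pre- versus post-intervention difference in adherence proportion, with 95% CI, as the deciding analysis. Present the quarterly series, or a segmented model, as supportive.
- **Sample size:** define 'sequential period' as a phase or a quarter, and state sidedness. Say that the adherence power refers to the two-period comparison and not to an interrupted time series model. Restate the maintenance figure: about 72% two-sided with 45 per period, or at least 80% only if one-sided. Reconcile the 37% with the stated insertion rates in the same edit.

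The cost is a few sentences. No extra observations are required; raising maintenance to 54 per period would restore 80% two-sided, but that is optional. The downside is that the deciding comparison is not corrected for background trend, which the supportive quarterly series can show.
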